**Methods:**

INFORM (Improving Nursing Home Care through Feedback On PerfoRMance Data) is a 3.5-year pragmatic, three-arm, parallel, cluster-randomized trial. We will randomize 67 Western Canadian nursing homes with 203 care units to the three study arms, a standard feedback strategy and two assisted and goal-directed feedback strategies. Interventions will target care unit managerial teams. They are based on theory and evidence related to audit and feedback, goal setting, complex adaptive systems, and empirical work on feeding back research results. The primary outcome is the increased number of formal interactions (e.g., resident rounds or family conferences) involving care aides – non-registered caregivers providing up to 80% of direct care. Secondary outcomes are a) other modifiable features of care unit context (improved feedback, social capital, slack time) b) care aides’ quality of worklife (improved psychological empowerment, job satisfaction), c) more use of best practices, and d) resident outcomes based on the Resident Assessment Instrument – Minimum Data Set 2.0. Outcomes will be assessed at baseline, immediately after the 12-month intervention period, and 18 months post intervention.

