##### Residents

We will obtain resident data from the RAI-MDS 2.0, which is used internationally for comprehensive geriatric assessment of the health, physical, mental, and functional status of nursing home residents [61]. In Canada its use is mandated in several provinces/territories, as well as by the Canadian Institute of Health Information for national reporting [120]. Data for calculating QIs are captured in quarterly assessments completed on all residents [121]. The two practice sensitive (i.e., modifiable by care staff) QIs [122] worsening pain and declining behavioural symptoms will form the focus at unit and facility levels.

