#### Secondary analyses

We will monitor change of secondary outcomes over time in each study arm, and compare outcomes between three study arms using descriptive statistics, statistical process control methods and appropriate significance tests (t tests for normally distributed, linear, continuous outcomes; non-parametric tests for variables that do not meet these assumptions; chi-squared tests for categorical outcomes). We will longitudinally track two practice sensitive RAI QIs (worsening pain, declining behavioural symptoms), using statistical process control methods [125–128]. We will calculate risk-adjusted and unadjusted indicators and, using control charts, graphically display unit and facility performances. These data will enable us to assess possible effects of *INFORM* on resident care as measured by resident QIs at a time consistent with the intervention. We will assign a dichotomous variable (*improved/not improved*) to each unit in the intervention. Then, using logistic regression with *improvement* as the outcome we will investigate the effects of context (using ACT scales), best practice use, and staff characteristics on improvement. To this end we have developed a reliable classification system for individual control charts [49, 50].

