## Discussion

INFORM is the first study to systematically assess effectiveness of different strategies to feed back research-based performance data to nursing home care units in order to improve their performance. In TREC we collect comprehensive longitudinal data on nursing home and care unit structural characteristics; modifiable features of nursing home and care unit work contexts; care providers’ use of best practices, health and quality of worklife; and various resident outcomes based on the RAI-MDS 2.0. Systematic feedback of these research data has been an important part of the long term TREC program. With INFORM we will be able to not only feed back data, but to systematically and comprehensively assess the most effective and cost-effective way to do so.

Our feedback interventions are based systematically on theory and evidence related to audit and feedback in the health care and organizational literature, goal setting, complex adaptive systems, and our own experiences with feeding back research results. This addresses Ivers and colleagues’ urgent call for systematic use of theory in future audit and feedback studies [129–131]. Furthermore, in order to determine which approaches to audit and feedback are most likely to change behaviours and improve performance, and to understand why these approaches work, head-to-head comparisons of different audit and feedback approaches, rather than comparison of audit and feedback with no intervention, are needed [129, 130].

We hypothesize that BAF and EAF will be significantly more effective than SF in improving formal interactions, context overall, and care provider as well as resident outcomes on nursing home care units. We furthermore expect that BAF and EAF will be similarly effective in doing so. However, we expect BAF to be more cost-effective than EAF. Results of this study will enable us to develop a practical, sustainable, effective, and cost-effective assisted feedback strategy that managers and policy makers can routinely use to improve performance of nursing home care units.

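### The between-arm comparison of the resident quality indicators rests on t, non-parametric and chi-squared tests that cannot meet the plan's own clustering and adjustment rules, and the only regression specific to these indicators lists no arm term

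*Protocol article*

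**What the plan says.** All references are to the protocol article.

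- The Abstract (Methods) lists among the secondary outcomes "resident outcomes based on the Resident Assessment Instrument – Minimum Data Set 2.0". In the Discussion the authors expect both assisted arms to outperform SF, and the hypothesis covers "improving formal interactions, context overall, and care provider as well as resident outcomes on nursing home care units".
- Under Residents, two QIs are singled out, worsening pain and declining behavioural symptoms. "Data for calculating QIs are captured in quarterly assessments completed on all residents".
- Secondary analyses opens with the between-arm plan: the team will "compare outcomes between three study arms using descriptive statistics, statistical process control methods and appropriate significance tests". The tests named are t tests, non-parametric tests and "chi-squared tests for categorical outcomes".
- The same section then follows the two QIs over time on control charts, risk-adjusted and unadjusted, for units and facilities. The stated purpose is to look for possible effects of INFORM on resident care.
- After that comes a classification: "We will assign a dichotomous variable" (improved or not) to each unit in the intervention. A logistic regression then takes improvement "as the outcome we will investigate the effects of context (using ACT scales), best practice use, and staff characteristics on improvement". Study arm is not among the listed terms.
- Controlling for potential biases commits the analysis to handling repeated measures within units and clustering of units within facilities. It also commits to adjusting all analyses for region, owner-operator model and facility size.
- Primary analysis uses mixed-effects regression, for the Formal Interactions (FI) score.

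**The concern.** Facilities were randomised, units sit within facilities, and the QIs recur every quarter. A test of BAF or EAF against SF on a QI has to respect both layers of dependence. Otherwise its standard error is too small and its p-value too optimistic. The primary outcome gets a model that does this. For the QIs, the tests named for the arm comparison do not.

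The section does contain a regression for the QIs, but it asks what predicts improvement and lists no arm term. A reader looking for the model behind the resident-outcome hypothesis therefore finds two candidates: simple tests at odds with the plan's own rules, and a model of something else. At stake is whether a claim that assisted feedback improved, or did not improve, resident care would rest on a valid randomised contrast.

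**Working it through.** **Step 1. Set each planned QI analysis against what the contrast needs.**

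| Analysis in Secondary analyses | Contrasts BAF/EAF with SF? | Handles facility clustering and repeated quarters? | Carries region, owner-operator model, size? |
|---|---|---|---|
| t, non-parametric, chi-squared tests | Yes | Not in standard form | No |
| Control charts | Named as one means of comparing arms; as described for the QIs, they display each unit's or facility's own course | They follow the series but give no arm estimate | No |
| Logistic regression on the improvement flag | No arm term listed | Not stated there; the general rule may be meant to cover it | Not listed; the general rule may be meant to cover it |

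No row meets all three needs. Controlling for potential biases stands beside Primary analysis and Secondary analyses under one Statistical analysis heading, and its adjustment rule covers all analyses. This is therefore a conflict in the stated text, not an omission.

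**Step 2. Size of the clustering problem.** The article gives no power figure, effect size or intraclass correlation (ICC) for the QIs, so there is nothing to reproduce. What follows is illustration on assumed values.

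Inputs: 203 units in 67 facilities (Inclusion and exclusion criteria), so 203/67 = 3.03, taken as 3 (also the average cluster size in Sample size calculation). ICC assumed at 0.1, 0.332 and 0.445. The last is the article's stated value for FI. The middle one follows from the article's FI standard deviations: 0.154² / (0.154² + 0.104² + 0.192²) = 0.0237/0.0714 = 0.332. Neither is a QI value.

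Design effect = 1 + (3 − 1) × ICC. True type I error of an unclustered two-sided 5% test = 2 × [1 − Φ(1.96/√design effect)].

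- ICC 0.1: design effect 1.20; 1.96/1.095 = 1.79; error about 7%.
- ICC 0.332: design effect 1.66; 1.96/1.290 = 1.52; error about 13%.
- ICC 0.445: design effect 1.89; 1.96/1.375 = 1.43; error about 15%.

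This covers facility clustering only, with one value per unit. If quarterly values were entered as separate observations, correlation within a unit would inflate the error further. The article gives no figure for that correlation.

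**Step 3. What dichotomising would cost if the arm comparison were run on the flag.** The chi-squared provision for categorical outcomes would allow this, though the article does not say it is intended. Assumptions: a normal unit-level score, a shift of d = 0.5 SD, a cut at which 20% or 50% of control units improve, two-sided alpha 0.05, and n per arm = (203/3)/(1 + 2 × ICC).

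- Continuous: power = Φ(d√(n/2) − 1.96). At ICC 0, n = 67.7: Φ(2.908 − 1.96) = 0.829.
- Flag: p₂ = Φ(Φ⁻¹(p₁) + d); power from the two-proportion normal formula with pooled variance under the null. At ICC 0, p₁ = 0.20, p₂ = 0.366: 0.576.

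| ICC | n per arm | Continuous | Flag, 20% | Flag, 50% |
|---|---|---|---|---|
| 0 | 67.7 | 0.829 | 0.576 | 0.624 |
| 0.1 | 56.4 | 0.756 | 0.500 | 0.545 |
| 0.332 | 40.7 | 0.616 | 0.382 | 0.419 |
| 0.445 | 35.8 | 0.562 | 0.343 | 0.376 |

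The loss runs from 0.562 − 0.376 = 0.186 to 0.756 − 0.500 = 0.256, about 19 to 26 percentage points. Power falls, but a comparison remains possible.

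**The case against.** The strongest reply is that the article does plan a randomised comparison. Secondary analyses opens with it, and the resident outcomes are secondary outcomes. The QI series is also retained on control charts, so it is not simply reduced to a flag. And the logistic model is explanatory: its stated aim is to find what goes with improvement, and nothing says its coefficients are effects of INFORM. All of this stands. A reader might infer that the plan cannot answer its resident-outcome hypothesis; the opening sentence of Secondary analyses rules that out.

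Three other strong readings also fail:

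- That the predictors are post-randomisation mediators. Their timing is not stated, and context is surveyed at baseline as well as later (Table 1).
- That SF units are left out of the classification. The wording is loose, but Table 1 and the sample-size model both count SF among the interventions.
- That a fixed share of information is lost. The textbook 2/π for a median split does not describe a control-chart classification whose rules are not shown.

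It can also be said that the general rule on clustering is meant to govern the secondary tests, and that model detail belongs in an analysis plan not shown here. A t test on facility-level summaries would indeed be valid for clustering, and the article mentions facility-level QIs. But the text does not say the tests will be done that way, and a plain t, rank or chi-squared test still cannot carry the promised adjustment. The article chose to name its tests, so the conflict lies in what it states.

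**Conclusion.** The point holds in this form: a between-arm comparison of the QIs is planned, but by tests that in standard form cannot meet the plan's own rules on clustering, repeated measures and adjustment. The only QI-specific regression has a dichotomised outcome and no listed arm term, so it cannot fill the gap.

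The size depends on unstated quantities. Under assumed ICCs of 0.1 to 0.445 and three units per facility, an unclustered test would have a type I error of about 7% to 15% instead of 5%. If the flag also served as the arm outcome, power might fall by 19 to 26 points at d = 0.5 under the assumptions shown; that is conditional, since the plan does not say so. The primary outcome is not affected. This should be changed before analysis, because a stated hypothesis depends on it.

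**What to change.** For each of the two QIs, make the arm comparison a mixed model of unit-by-quarter rates, either binomial or linear on the risk-adjusted rate. Include time, arm-by-period terms for BAF and EAF versus SF, region, owner-operator model and size, and random effects for facility and unit. Include the SF units explicitly. This extends to the QIs the approach already chosen for FI, and it brings Secondary analyses into line with Controlling for potential biases.

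Keep the control charts as display. Label the improved/not-improved logistic regression exploratory, with standard errors clustered by facility. State when its predictors are measured and that units from all three arms are classified, if that is the intention.

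The cost is analysis work on data already being collected: more modelling than simple tests and a chart classification, but no new data, participants or visits.

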## Discussion

INFORM is the first study to systematically assess effectiveness of different strategies to feed back research-based performance data to nursing home care units in order to improve their performance. In TREC we collect comprehensive longitudinal data on nursing home and care unit structural characteristics; modifiable features of nursing home and care unit work contexts; care providers’ use of best practices, health and quality of worklife; and various resident outcomes based on the RAI-MDS 2.0. Systematic feedback of these research data has been an important part of the long term TREC program. With INFORM we will be able to not only feed back data, but to systematically and comprehensively assess the most effective and cost-effective way to do so.

Our feedback interventions are based systematically on theory and evidence related to audit and feedback in the health care and organizational literature, goal setting, complex adaptive systems, and our own experiences with feeding back research results. This addresses Ivers and colleagues’ urgent call for systematic use of theory in future audit and feedback studies [129–131]. Furthermore, in order to determine which approaches to audit and feedback are most likely to change behaviours and improve performance, and to understand why these approaches work, head-to-head comparisons of different audit and feedback approaches, rather than comparison of audit and feedback with no intervention, are needed [129, 130].

We hypothesize that BAF and EAF will be significantly more effective than SF in improving formal interactions, context overall, and care provider as well as resident outcomes on nursing home care units. We furthermore expect that BAF and EAF will be similarly effective in doing so. However, we expect BAF to be more cost-effective than EAF. Results of this study will enable us to develop a practical, sustainable, effective, and cost-effective assisted feedback strategy that managers and policy makers can routinely use to improve performance of nursing home care units.

### Trial status

We have started recruitments of facilities and managerial teams on March 01, 2016, and recruitment is ongoing.
